### Intervention program

After the first visit, participants and their spouses will be entered into a run-in period for 4 weeks in which their regularly consumed oils will be replaced with sunflower oil. During the run-in period, the participants will be randomly assigned to one of the 6 rolling sequences (Fig. 1). The participants will be asked to replace the oils regularly used at home with the intervention oils. All measurements and blood sampling will be done at the beginning and the end of each intervention period, therefore, there will be 8 visits. The details of all measurements that will be conducted during each visit are provided in Table 1.

**Table 1 Tab1:** Details of study visits

Measured variables	Beginning of study	Beginning of the run-in period	Beginning of phase 1	End of phase 1	Beginning of phase 2	End of phase 2	Beginning of phase 3	End of phase 3
	Visit 1	Visit 2	Visit 3	Visit 4	Visit 5	Visit 6	Visit 7	Visit 8
**Eligibility criteria assessment**	*							
**Medical history**	*							
**Informed consent**	*							
**Nutrition counseling**	*							
**Medication use**	*	*	*	*	*	*	*	*
**Physical activity**	*	*	*	*	*	*	*	*
**24-h dietary recall**	*	*	*	*	*	*	*	*
**Anthropometric measurement**	*		*	*	*	*	*	*
Weight	*		*	*	*	*	*	*
Height	*		*	*	*	*	*	*
Waist circumference	*		*	*	*	*	*	*
Hip circumference	*		*	*	*	*	*	*
**Body composition indices**			*	*	*	*	*	*
Body fat mass			*	*	*	*	*	*
Lean mass			*	*	*	*	*	*
Visceral fat			*	*	*	*	*	*
**Blood pressure**	*	*	*	*	*	*	*	*
**Blood sampling**			*	*	*	*	*	*
**Biochemical assessment**			*	*	*	*	*	*
Fasting blood glucose (FBS)	*		*	*	*	*	*	*
Triglyceride (TG)	*		*	*	*	*	*	*
High-density lipoprotein (HDL)	*		*	*	*	*	*	*
Total antioxidant capacity (TAC)			*	*	*	*	*	*
Total oxidant status (TOS)			*	*	*	*	*	*
Malondialdehyde (MDA)			*	*	*	*	*	*
Myeloperoxidase (MPO)			*	*	*	*	*	*
Superoxide dismutase (SOD)			*	*	*	*	*	*
Catalase (CAT)			*	*	*	*	*	*
Glutathione peroxidase (GPX)			*	*	*	*	*	*
Glutathione reductase (GR)			*	*	*	*	*	*
Nitric oxide (NO)			*	*	*	*	*	*

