### Physical activity and dietary intake assessment

The participants will be asked to keep their physical activity level and dietary intake constant during the study. The participant’s physical activity will be assessed using 3-day physical activity records (2 weekdays and 1 day of the weekend). The 3-day physical activity records will be filled in 6 times during the study (at the beginning and end of each intervention phase) (Table 1). The recorded data will be converted into metabolic equivalent-min/day (MET-minute/day) using the updated version of the compendium of physical activities [35]. Three-day dietary recalls (2 weekdays and 1 day of the weekend) will be used to measure dietary nutrient intake, including macro and micro-nutrients, at the beginning and the end of each phase of the intervention.

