### Statistical analyses

The statistical analysis will be performed using STATA software (version 14, TX, 77,845 USA). The normal distribution of the quantitative data will be determined using the Kolmogorov–Smirnov test, and the skewed variables will be normalized by transformation before analysis. The effects of treatment oils will be compared using the linear mixed method with the rolling process between-subject factors. Effect sizes will be adjusted by the potential confounders including age, sex, baseline BMI, the number of intervention oils consumed per subject, physical activity as metabolic equivalent-min/day, and the amount of calorie intake as covariates. Also, we will be performed subgroup analysis for sex. We will use the intention-to-treat method to handle protocol for those with non-adherence. No interim analysis is planned for this study because no early confirmatory conclusion of the effect of intervention oils can be drawn before the end of the study and enrollment of all participants. To control the carryover effect, clinically, an appropriate washout period will be considered (1 month). However, the carry-over effect will also be statistically tested through the mixed effect model. Any missing data will be handled using multiple imputations according to Harrell’s guidelines [36].

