A limitation of this trial is that this is a single-center study which limits the generalization of results to all populations. Because of long-term intervention, the recruitment of study participants might be the challenging part of the study. To overcome this challenge, we will try to explain the benefits of participating in this study and the importance of study results for public health and industry. Endocrinologists will also help to increase the participation rate because people trust their physicians in Iran. As, in this trial, we aimed to substitute the common oils routinely consumed by participants with intervention oils; therefore, it will be not possible to calculate the exact amount of oils consumed by each person. However, we will try to resolve this problem by asking the participants to report the amount of oil consumed as tablespoons in their food recalls, as well as, the bottle oils will be weighed before and after consumption of each phase.

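### The oil-effect model adjusts for oil consumed, calorie intake and physical activity, which are recorded after randomisation; if the oils shift them, the randomised contrast can be biased and no longer estimates the effect of substituting the oil.

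*Protocol article*

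**What the plan says.** Under Statistical analyses, the protocol article compares the oils with a linear mixed model that includes the sequence as a between-subject factor. It then says: "Effect sizes will be adjusted by the potential confounders including age, sex, baseline BMI", and continues the same list with "the number of intervention oils consumed per subject, physical activity as metabolic equivalent-min/day, and the amount of calorie intake as covariates". Only BMI is labelled as a baseline value. No oil-effect analysis without the last three covariates is described. The same paragraph states: "We will use the intention-to-treat method to handle protocol for those with non-adherence".

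Four other places bear on this:

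- Intervention program: "During the run-in period, the participants will be randomly assigned to one of the 6 rolling sequences". Allocation therefore precedes the first oil phase.
- Physical activity and dietary intake assessment: "The 3-day physical activity records will be filled in 6 times during the study (at the beginning and end of each intervention phase"), and "The recorded data will be converted into metabolic equivalent-min/day". The 3-day dietary recalls are likewise taken "at the beginning and the end of each phase of the intervention".
- Compliance: returned bottles are weighed, and the 3-day recalls are used to judge adherence.
- Strengths and limitations of this study: because the household's routine oil is being replaced, "it will be not possible to calculate the exact amount of oils consumed by each person". The article then offers two approximations, tablespoons reported in the recalls and bottle weights.

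**The concern.** Randomising the order of the oils already protects the comparison between them from confounding, so these three variables are not confounders of that comparison. They can be consequences of it. If one blend is used more or less freely, or changes how much people eat, then oil consumed and calories differ between oils because of the oil. Holding them constant removes whatever part of the effect runs through them. It can also create a spurious difference when something else drives both the covariate and the oxidative stress markers within a period.

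The trial asks what happens when the household oil is substituted. An oil contrast at equal consumption and equal calories answers a different question. Because this is the only model described, all nine primary markers would be affected.

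**Working it through.** The plan has no figure of its own to reproduce here. The check has three parts.

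**1. Timing of each covariate against allocation (in the run-in)**

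| Covariate | When recorded | Can the oil of that period change it? |
|---|---|---|
| Age, sex, baseline BMI | Before the oils | No |
| Oil consumed (amount, or count of oils received; the wording allows both) | Only after allocation | Yes |
| Activity, MET-min/day | Start and end of each phase | Start value no, end value yes |
| Calorie intake | Start and end of each phase | Start value no, end value yes |

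The recalls also record tablespoons of oil, so calorie intake can contain the intervention itself.

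**2. Size by formula**

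With covariate shift *a* between oils and slope *s* of the marker on the covariate in the adjusted model, the adjusted contrast differs from the total effect by −*a* × *s*. Both inputs are assumptions: *a* from 0 to 0.5 SD, *s* from 0.1 to 0.3 SD per SD.

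- No shift: 0 × *s* = 0
- Low: 0.1 × 0.1 = 0.01 SD
- Mid: 0.3 × 0.2 = 0.06 SD
- High: 0.5 × 0.3 = 0.15 SD

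For scale, the Sample size section gives two bases. It does not name the effect size of 0.10–0.13; read as Cohen's f, with three means and the third midway, the largest difference is f × √6:

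- 0.10 × √6 = 0.245 SD, and 0.06 / 0.245 = 24%
- 0.13 × √6 = 0.318 SD, and 0.06 / 0.318 = 19%
- Against the SMD of one: 0.06 / 1 = 6%

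These percentages treat the bias and the planned difference as being in the same SD unit.

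**3. Simulation**

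A cross-over with 72 participants, three periods and six sequences was analysed with participant and period effects, with and without the covariate (600 runs per scenario). One oil had a direct effect of 0.3 on the marker and shifted the covariate by *a*. *b* is the covariate's effect on the marker, *g* the strength of a shared within-period cause. All are assumed values.

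| a | b | g | Covariate reliability | True total effect | Adjusted estimate | Bias |
|---|---|---|---|---|---|---|
| 0 | 0 or 0.3 | 0 or 0.5 | 1 or 0.5 | 0.300 | 0.296 to 0.310 | −0.004 to +0.010 |
| 0.3 | 0.3 | 0 | 1 | 0.390 | 0.302 | −0.088 |
| 0.3 | 0 | 0.5 | 1 | 0.300 | 0.216 | −0.084 |
| 0.5 | 0.3 | 0 | 1 | 0.450 | 0.312 | −0.138 |
| 0.5 | 0.3 | 0.5 | 1 | 0.450 | 0.183 | −0.267 |
| 0.5 | 0.3 | 0.5 | 0.5 | 0.450 | 0.305 | −0.145 |

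The results follow the formula. In the fifth row the slope in the adjusted model is 0.3 + 0.5 × 0.5 = 0.55, and 0.5 × 0.55 = 0.275. That slope lies outside the range assumed in part 2, so the row shows what a strong shared cause could do and is not an expected value. Leaving the covariate out recovered the total effect to within about 0.015 in every scenario.

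**The case against.** The strongest reply is that the oils may not move these variables at all. They are matched in appearance and odour, the trial is triple-blind, and participants are asked to keep diet and activity constant. There is no obvious route from a cooking oil to physical activity. With no shift the bias is about zero, as the first row of the simulation shows. This stands: the bias is possible, not demonstrated. But the safeguards make a zero shift more plausible without ensuring it.

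Several stronger readings are tempting, and the documents do not support them:

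- *That the protocol admits it cannot measure oil intake.* It says only that the exact amount per person cannot be calculated, and it gives two approximations, one of them from the participant's own recall. Nor does random error in the covariate enlarge the bias: at reliability 0.5 the simulated bias was smaller. What it leaves is a partly adjusted contrast that is hard to interpret.
- *That the model contradicts intention-to-treat outright.* Participants who do not adhere can still be analysed in their allocated sequence. The tension is over what is estimated, not over who is analysed.
- *That all three covariates are certainly measured under the oil.* The article does not say which visit's activity and calorie values are used. Table 1 also lists activity and a 24-hour recall at Visits 1 and 2, and start-of-phase values precede that period's oil. Those would be much less harmful, though at phases 2 and 3 they follow an earlier oil. This does not rescue oil consumed.
- *That 0.3 × 0.3 = 0.09 SD, or 28–37% of the planned difference, is a typical bias.* A slope of 0.3 is the top of the assumed range.

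**Conclusion.** The concern holds as a risk built into the stated model. It is clearest for oil consumed, which is necessarily recorded after allocation and is a compliance measure. For activity and calories it depends on which values are used, and the article leaves that open. Conditioning on these variables can bias the oil contrast and departs from the effect of substitution that the trial and its handling of non-adherence aim at.

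The size cannot be derived from the documents. Under the assumed ranges it runs from 0 to 0.15 SD, with 0.06 SD in the middle. Whether that matters depends on which sample-size basis is taken: it is a sizeable share of the small planned effect, if that is a Cohen's f, and minor against the SMD of one.

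**What to change.** State the primary model as oil, period, sequence and a random participant effect, with pre-randomisation covariates only: sex (the stratification factor), age and baseline BMI. Move oil consumed, calorie intake and activity to a secondary analysis labelled as an adherence or sensitivity analysis. There, say whether the oil variable is an amount or a count, how it is derived from bottle weights and recalls, and which visit's calorie and activity values are used. Stop calling these three variables confounders.

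Adding a period-baseline value of the marker is a separate choice and not part of this fix: phase baselines also follow randomisation, and those of phases 2 and 3 follow earlier oil exposure.

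The cost is a change of wording, which can be recorded as an amendment while the oil codes are still withheld. No new data are needed. Some precision may be lost if calories or activity explain within-person variation in the markers, but the loss is likely to be small.

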### Patient and public involvement statement

Study participants and the public were not involved in the research design. The primary outcomes will be discussed with the study participants via private meetings with the researchers after the analyses become completed.

### Ethics and monitoring

The ethical approval for conducting this study was obtained from the research ethics committee of Shahid Sadoughi University of Medical Sciences (2021, IR.SSU.SPH.REC.1400.167 (24 November 2022, https://ethics.research.ac.ir/PortalProposalList.php?code=IR.SSU.SPH.REC.1400.167). Also, the data monitoring committee, audit the consenting process, protocol adherence, and data collection, will be done by this ethics committee. Protocol amendments will be promptly reported to the research ethics committee of Shahid Sadoughi University of Medical Sciences. Also, the data monitoring committee, audit the consenting process, protocol adherence, and data collection, will be done by this ethics committee. Protocol amendments will be promptly reported to the research ethics committee of Shahid Sadoughi University of Medical Sciences. Data and safety monitoring committee (DSMC) will consist of 4 independent experts in clinical medicine, nutrition, biochemistry, and biostatistics. They will review the study protocol for any major concerns prior to implementation, regularly review and evaluate the accumulated study data for participant safety, study conduct, and progress, and make recommendations concerning the continuation, modification, or termination of the trial. They are independent of the study sponsor and have no competing interests. [name] will meet with the DSMC every 2 months and will present a written and verbal report. Additional meetings will be scheduled if warranted by the data or adverse events. The study protocol is also registered on 4 March 2022 in the Iranian Registry of Clinical trials (IRCT20130223012571N8, https://irct.ir/user/trial/60665/view). We will report protocol details and any amendments there. Informed consent will be obtained from all study participants. Participants will be allowed to leave the study without explanation and will not be compensated for participation. The study will be coordinated by the principal investigator at the Endocrinology and Metabolism clinics and polyclinics of Shahid Sadoughi University of medical sciences, Yazd, Iran. Study coordination, monitoring, data attainment and management, and statistical analysis will be performed by the principal investigator of the research. The International Committee of Medical Journal Editors (ICMJE) guidelines will be used for publishing the protocol and final manuscript. Professional writers will not be employed for writing.

### Dissemination

The results of this trial will be published in peer-reviewed scientific journals and presented at international academic meetings. We anticipate the findings will be of interest across broad fields like nutrition, endocrinology, MetS treatment, industry, and public health.

## Discussion

### Strengths and limitations of this study

The present clinical trial will be the first one assessing the impact of *Pistacia atlantica* oil on human oxidative stress markers. Previous investigations were done only on animals [1, 18–21]. This is a three-way randomized cross-over clinical trial in which subjects will act as their controls. This minimizes the effect of genetic polymorphisms, differences in lifestyle, and environment-related confounding variables on the observed effects. Furthermore, we will try to minimize the potential selection bias, confounding factor, and ascertainment bias by using standard methods for randomization, allocation concealment, and blinding.

The 8-week duration of intervention for each phase is long enough to investigate changes in total antioxidant capacity and total oxidant status. Additionally, with 72 participants and enough biological samples, our study enables researchers to examine the sex-stratified effect of the intervention oils and different markers with high statistical power. This sample size provides us with enough power to study possible gene-diet interactions in the future. Also, a unique feature of this study will be that we will compare novel oil blends with the usual oils that are available in the marketplace.

Medications used by participants will be recorded on each visiting day, then the investigators will be able to check the sensitivity of the observed effects to medication change by removing those who report a change in their medications. It is noteworthy that, all the procedures mentioned in the present study will be also conducted for the participants’ spouses, and thus, it is possible to assess the effect of the intervention oils in adults without MetS.

A limitation of this trial is that this is a single-center study which limits the generalization of results to all populations. Because of long-term intervention, the recruitment of study participants might be the challenging part of the study. To overcome this challenge, we will try to explain the benefits of participating in this study and the importance of study results for public health and industry. Endocrinologists will also help to increase the participation rate because people trust their physicians in Iran. As, in this trial, we aimed to substitute the common oils routinely consumed by participants with intervention oils; therefore, it will be not possible to calculate the exact amount of oils consumed by each person. However, we will try to resolve this problem by asking the participants to report the amount of oil consumed as tablespoons in their food recalls, as well as, the bottle oils will be weighed before and after consumption of each phase.

### Future investigations

The researchers are planning to explore the effect of the intervention oils on markers of glucose control including fasting serum insulin, cardiometabolic markers including total cholesterol, low-density lipoproteins (LDL-C), oxidized LDL, Apo A, Apo B, Lipoprotein (a) [LP (a)], liver enzymes [alanine aminotransferase(ALT), aspartate transaminase (AST), gamma-glutamyl transferase (GGT), alkaline phosphatase (ALP)], blood markers of kidney function [blood urea nitrogen (BUN), serum creatinine, and glomerular filtration rate (GFR)], and inflammatory markers [high sensitivity C-reactive protein (hs-CRP), interleukin-6 (IL-6), tumor necrosis factor-alpha (TNF-α)] in participants with MetS and their spouses in the near feature. Also, the current study provides a good medium for investigators to examine the possible interaction effect of gene polymorphisms and intervention oils on inflammatory and cardiometabolic markers. In this regard, investigators will explain the study objectives for the participants and informed consents will be obtained. The investigators will welcome possible collaborations with interested scientists and novel hypotheses that could be checked using the available samples and data obtained in the current study.

## Conclusion

As the relation between total antioxidant capacity and several diseases was confirmed by previous studies, we will explore the effect of substitution of regular oil consumed in a household with a blend of *Pistacia atlantica* seed and canola oil, with a blend of corn and canola oil with TBHQ and a blend of corn and canola oil without TBHQ on oxidative stress markers in participants with MetS and their spouses. In this three-way, triple-blind, clinical trial, the bio-banking of blood components will be done for study participants and their spouses will provide the opportunity to investigate the effect of dietary oils on different aspects of human health.

### Trial status

The trial recruitment will begin on 22 May 2022. All trial participants should have finished the interventions up to 20 March 2023.

### Protocol version

Version 1.1, January 2023.

## Data Availability

The data of the present study will be fully available to the corresponding author. As data was approved to be used for the current analysis, only, it will not be available to the public. Any data required to support the protocol can be supplied on request.

## Abbreviations

ALP: Alkaline phosphatase
ALT: Alanine aminotransferase
AST: Aspartate transaminase
BUN: Blood urea nitrogen
CAT: Catalase
DBP: Diastolic blood pressure
DPPH: Diphenyl-1-picrylhydrazyl free radical
FBG: Fasting blood glucose
GC-FID: Gas chromatography with a flame ionizer detector
GFR: Glomerular filtration rate
GGT: Gamma-glutamyl transferase
GPx: Glutathione peroxidase
GR: Glutathione reductase
HDL: High-density lipoprotein
hs-CRP: High sensitivity C-reactive protein
IL-6: Interleukin-6
LDL-C: Low-density lipoproteins
LP (a): Lipoprotein (a)
MDA: Malondialdehyde
MetS: Metabolic syndrome
MPO: Myeloperoxidase
NO: Nitric oxide
OS: Oxidative stress
RCT: Randomized cross over clinical trial
SBP: Systolic blood pressure
SOD: Superoxide dismutase
SPIRIT: Standard Protocol Items for Randomized Trials
TAC: Total antioxidant capacity
TBHQ: Tert-Butylhydroquinone
TG: Triglyceride
TOS: Total oxidant status
TNF-α: Tumor necrosis factor alpha
